### Statistical analysis

Categorical variables were presented as percentages and continuous variables as mean with standard deviation (SD) or median with interquartile range (IQR). In univariable analyses, *t* test or Mann–Whitney test will be used to compare continuous variables, whereas *χ*2 test or Fisher’s exact test will be used to compare the categorical variables. Multivariable logistic regression will be used to evaluate the predictors of hemorrhage and long-term neurological outcomes in the cross-sectional dataset, and ORs with their 95% CIs will be evaluated. Univariable and multivariable Cox proportional hazard regression model or competing risk analysis or NCC will be performed to explore the predictors of subsequent hemorrhage in the survival dataset, and HRs with their 95% CIs will be evaluated. Kaplan–Meier plots of time-to-event outcomes of subsequent hemorrhage or complete obliteration (for AVMs who underwent SRS) among different treatment modalities will be presented. Generalized linear models or generalized linear mixed models will be used to explore potential correlates for continuous dependent prognostic parameters. Receiver operating curves (ROCs) will be used to assess the predictive validity in constructing predictive models for subsequent hemorrhage or long-term neurological outcomes. In cohort studies, propensity score matching (PSM) and inverse probability of treatment weighted (IPTW) will be used to adjust for confounding factors. Statistical significance was set at *p* < 0.05 (two-sided).

In this article, we compared the baseline demographic, clinical, and angioarchitecture characteristics of the multi-disciplinary and single-disciplinary assessment groups. Besides, although quality control has been maximized through the EDC system, there are still some missing values (less than 2%), which we have also reported. Proportions were used to describe the categorical variables, and means with SD or median with the IQR were used for continuous variables. Statistical analysis was performed using SPSS (version 25.0, IBM, New York, USA).

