### Study objectives

The objectives of the MATCH study were to identify the natural history of AVMs in the Asian population; to investigate the traditional and emerging angioarchitecture, hemodynamic, genetic, and environmental risk factors associated with AVM rupture; and to explore the superiority of the multidisciplinary assessment in improving the long-term outcomes. Based on this, individualized rupture and prognostic prediction models will be established to promote the precision medicine.

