### Patient enrollment

All AVMs diagnosed at participating hospitals will be candidates for this study, which is expected to include approximately 4000 AVMs between August 1, 2011 and April 1, 2032. The inclusion criteria are as follows: (1) the diagnosis of AVM is confirmed with digital subtraction angiography (DSA) and/or magnetic resonance imaging (MRI); (2) patients with complete clinical and imaging data; (3) patients or their guardians agree to collect personal information for this study and sign informed consent. The exclusion criteria are as follows: (1) patients undergo intervention management before admission, such as microsurgery, embolization, or SRS; (2) patients diagnosed with spinal AVMs; (3) patients missing critical baseline demographic, clinical, and imaging data.

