### Demographic and clinical characteristics

The demographic data included sex, ethnicity, admission age, family history, diet, physical activity, educational attainment, lifestyle, smoking status, drinking status, and medication history.

The clinical characteristics included onset manifestation (hemorrhage, seizure, headache, neurofunctional deficit, accidentally discovered, others), admission modified Rankin Scale (mRS), time of each rupture, treatment modalities (conservation, microsurgery, embolization, SRS, multimodality strategy, etc.), discharge obliteration rate, perioperative complications (hemorrhage, seizure, intracranial infection, etc.), discharge mRS, etc. The hemorrhagic presentation is defined as hemorrhage attributable to AVM rupture with symptomatic and CT evidence. Seizure is classified as generalized and partial. The evaluation of mRS was conducted by trained who have at least 5 years of experience in clinical practice.

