**Fig. 2 Fig2:**
[figure not shown]
Flow chart of patients’ enrollment in MATCH. AVM, arteriovenous malformation; MATCH, registry of multimodality treatment for brain arteriovenous malformation in mainland China; SRS, stereotactic radiosurgery

**Table 2 Tab2:** Baseline characteristics of included and excluded AVMs in the MATCH study

Characteristics	Included	Excluded	*P* value
Baseline demographic data	*N* = 3241	*N* = 412	
Sex, male, n (%)	1911 (59.0)	240 (58.3)	0.782
Age (years)			
Mean ± SD	28.4 ± 14.6	28.3 ± 12.2	0.831
Baseline clinical data^a^	*N* = 3241	*N* = 371	
Onset manifestation			
Hemorrhage, n (%)	1984 (61.2)	226 (60.9)	0.911
Seizure, n (%)	754 (23.3)	84 (22.6)	0.858
Admission mRS			
Median, IQR	1 (1, 2)	1 (0, 2)	0.788
Baseline imaging data^b^	*N* = 3241	*N* = 316	
Location, supratentorial, n (%)	2844 (87.7)	281 (88.9)	0.542
AVM maximum diameter (cm)			
Mean ± SD	3.4 ± 1.9	3.3 ± 2.0	0.857
Eloquence, n (%)	1794 (55.3)	180 (56.9)	0.583
Deep venous drainage, n (%)	1284 (39.6)	122 (38.6)	0.726
Spetzler-Martin Grade			0.848
I-III	2694 (83.1)	264 (83.5)	
IV-V	547 (16.9)	52 (16.5)	

*AVM* Arteriovenous Malformation, *IQR* Interquartile Range, *N* Denominator, *n* numerator, *MATCH* Registry of Multimodality treatment for brain ArTeriovenous malformation in mainland China, *mRS* Modified Rankin Scale, *SD* Standard Deviation

^a^ 41 AVMs in the excluded cohort missing critical baseline clinical data

^b^ 96 AVMs in the excluded cohort missing critical baseline imaging data

Baseline demographic and clinical characteristics of the included AVMs are presented in Table 3. Overall, 59.0% were male, and the average age was 28.4 years. Among all enrolled patients, 61.2% (1984 cases) had rupture history, and 2268 rupture events occurred before admission. The median duration from diagnosis to treatment (including intervention and conservation) was 2.9 months. Microsurgery is the dominant treatment strategy (35.7%), 12.7% received endovascular embolization as monotherapy, and 14.8% underwent SRS. Staged embolization + SRS is the most common multimodal treatment strategy (11.8%). At the most recent follow-up, 7.8% were lost. The median follow-up duration was 5.6 years, and 79.4% have completed 3 years of follow-up. There were no statistically significant differences in all demographic and clinical characteristics between single-discipline and multidiscipline cohorts except for the follow-up duration.

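### The cross-sectional logistic regression of hemorrhage models mode of presentation in a cohort entered by diagnosis, so its odds ratios do not measure rupture risk alone

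*Protocol article*

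**What the plan says.** Protocol article, Statistical analysis: "Multivariable logistic regression will be used to evaluate the predictors of hemorrhage and long-term neurological outcomes in the cross-sectional dataset", reported as odds ratios with 95% confidence intervals. The next sentence sets out a different analysis, by Cox regression, competing-risk methods or nested case-control sampling, to "explore the predictors of subsequent hemorrhage in the survival dataset", reported as hazard ratios.

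Patient enrollment gives the route into the cohort: "All AVMs diagnosed at participating hospitals will be candidates for this study".

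Demographic and clinical characteristics lists hemorrhage as one of several onset manifestations, beside seizure, headache, deficit and chance discovery. It defines the baseline variable: "The hemorrhagic presentation is defined as hemorrhage attributable to AVM rupture with symptomatic and CT evidence". Results reports that "61.2% (1984 cases) had rupture history, and 2268 rupture events occurred before admission". Table 3 gives the same 1984 under onset manifestation.

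Study objectives says what the predictors are for: the registry is to investigate "hemodynamic, genetic, and environmental risk factors associated with AVM rupture".

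**The concern.** The article separates a cross-sectional dataset from a survival dataset and reserves subsequent hemorrhage for the latter. The hemorrhage modelled by logistic regression is therefore the one present at or before entry.

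That outcome is also one of the main reasons a patient is in the registry. The comparison group is not a sample of AVMs followed over time without bleeding. It consists of patients whose AVM came to light some other way. The model has no time at risk. A factor that makes an AVM more or less likely to be found without a bleed will shift the odds ratio even if it has no bearing on rupture.

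Timing adds a second problem. Table 1 schedules MRI and DSA at screening and before treatment, and hemodynamic evaluation from the pre-treatment visit. In a patient who presented with hemorrhage, all of these follow the bleed, so a change caused by the hemorrhage can be read as a factor that preceded it. The article presents the hemodynamic parameters as a strength, and they are exposed to this too.

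At stake is the second main objective. If odds ratios for presentation are reported under a label that calls them predictors, readers will take them as rupture risk factors. The limitations in the Discussion mention selection at hospital level but not this selection of patients.

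**Working it through.** **1. Reproduce the stated share.** Inputs from Results and Table 3: 1984 / 3241 = 0.6122, the stated 61.2%. By cohort, 1677 + 307 = 1984. Prior events, 1917 + 351 = 2268. Patients without hemorrhagic presentation: 3241 − 1984 = 1257.

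The onset categories in Table 3 overlap: 1984 + 754 + 698 + 583 + 271 = 4290, and 4290 / 3241 = 1.32. Hemorrhage is therefore *a* presenting manifestation in 61.2%, not necessarily the only one.

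**2. What the odds ratio estimates.** As a simplification, let a patient enter at the earlier of rupture (constant rate *h_r*) or detection by another route (constant rate *h_o*).

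- Probability of hemorrhagic presentation = *h_r* / (*h_r* + *h_o*), so the odds = *h_r* / *h_o*.
- If a factor multiplies *h_r* by RR_r and *h_o* by RR_o, then OR = RR_r / RR_o.

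The OR equals the rupture rate ratio only when RR_o = 1.

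**3. Numerical check.** The Background gives an untreated rupture rate of 1–3% per year. Setting *h_o* = *h_r* × (1 − 0.612) / 0.612 = 0.634 × *h_r* reproduces 61.2% hemorrhagic presentation in the reference group. For *h_r* = 2% this is *h_o* ≈ 1.27% per year. Logistic regression was run on 400,000 simulated patients per scenario, at *h_r* = 1%, 2% and 3%. RR_r and RR_o are assumptions; the article gives neither.

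| Effect on rupture (RR_r) | Effect on other detection (RR_o) | Expected OR | Simulated OR, range over the three rates |
|---|---|---|---|
| 1 | 1 | 1.0 | 0.998–1.001 |
| 1 | 2 | 0.5 | 0.495–0.504 |
| 1 | 0.5 | 2.0 | 2.003–2.024 |
| 2 | 2 | 1.0 | 1.006–1.018 |
| 2 | 4 | 0.5 | 0.499–0.503 |
| 2 | 1 | 2.0 | 1.986–2.000 |

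A factor with no effect on rupture can look harmful or protective. One that doubles the rupture rate can look neutral or protective. The result does not depend on the rupture rate assumed.

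**The case against.** The strongest reply is that the harm lies mostly outside this model. Study design and the Discussion assign the rupture prediction models to nested case-control studies, and the sentence on receiver operating curves ties hemorrhage prediction to subsequent events. The article already separates odds ratios in the cross-sectional dataset from hazard ratios in the survival dataset, and it already has the term hemorrhagic presentation. Much of what is needed is therefore planned, and what remains is how one analysis is labelled and read. This stands, and it limits the severity.

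Some stronger inferences are tempting but are not supported:

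- A reader might infer that these odds ratios feed the rupture model, and that patients would be mis-ranked when the multidisciplinary team uses such a model for unruptured AVMs. Clinical management does not say where that model comes from, and nothing says it comes from this regression.
- A reader might take odds ratios of 2.0 or 0.5 as the size of the bias. They only restate the assumed detection ratios, under a two-route model that overlapping onset categories make approximate.
- A reader might think propensity matching or weighting is offered as the remedy here. The article plans those methods for cohort comparisons only.

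The reply that interpretation belongs in a fuller document carries less weight. The article itself fixes the outcome and calls the results predictors, under an objective of finding "risk factors associated with AVM rupture". Nothing in it keeps these odds ratios from being reported as rupture risk factors.

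**Conclusion.** The concern holds for the hemorrhage outcome of the cross-sectional logistic model. It does not extend to the long-term neurological outcomes named in the same sentence, or to the survival and nested case-control analyses. The odds ratios reflect a factor's effect on rupture relative to its effect on detection by other routes, with imaging that follows the bleed in ruptured patients. It would go too far to say that they carry no information on rupture, since the rupture effect is one of the two components.

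The size cannot be given from the document. The illustration rests on constant rates, two entry routes and assumed detection ratios. The qualitative conclusion needs only that some factor under study affects how AVMs are found without bleeding. Severity is moderate: a wrong inference is invited on a main objective, but the planned longitudinal analyses offer a sounder basis and the rupture objective does not rest on this model alone.

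**What to change.** In Statistical analysis, rename the cross-sectional hemorrhage analysis *factors associated with hemorrhagic presentation*. State that its odds ratios are not reported as rupture risk factors and do not select or weight variables for the rupture model.

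Draw rupture-risk statements only from the planned survival or nested case-control analysis of hemorrhages after entry, and specify there:

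- imaging and hemodynamics taken before the event;
- rupture at entry as a covariate or stratum;
- follow-up restricted to untreated time, either censored at first intervention or with intervention handled as a competing event.

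The last item is needed because 3241 − 491 = 2750 patients (84.9%) were treated (Table 3). Hemorrhages after entry would otherwise mix rupture risk with treatment effect.

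**Cost.** No new data are needed, but there are far fewer events. As a rough guide, assume that the 491 conserved patients have the cohort's 5.6-year median follow-up (the article gives no separate figure) and treat that median as a mean: 491 × 5.6 ≈ 2750 person-years. At 1–3% per year this gives about 27 to 82 hemorrhages, plus those in pre-treatment intervals, against 1984 baseline cases. Intervals will be wider. Censoring at treatment may also be informative, because the choice to treat depends partly on perceived rupture risk; this should be acknowledged when the results are reported.

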### Clinical management

Conservation, microsurgery, embolization, SRS, and multimodal strategies are all included in this study. Patients will be divided into experimental and control groups according to whether the treatment protocols were formulated by a multidisciplinary team. In order to reduce workload, the MATCH Research Organizing Committee developed a standardized treatment protocol of multidisciplinary assessment as follows:

Ruptured AVMs: (1) microsurgery: microsurgery is recommended for AVMs not located in deep critical eloquent areas (brainstem, thalamus, basal ganglia, etc.) or more than 5 mm away from functional fiber bundles, regardless of the SM grade; (2) embolization: embolization should be performed 2–6 weeks after rupture; target embolization for hemorrhagic predictors could be considered as a monotherapy; palliative embolization can be used as an adjunctive strategy to reduce blood flow or nidus volume before microsurgery or stereotactic SRS; (3) SRS: SRS is indicated for patients with a nidus volume < 10 ml and not in the acute phase of hematoma (< 3 months); volume-stage or dose-stage can be used for giant AVMs. (4) Multimodality: the multimodality strategy such as single-stage combined embolization + resection (hybrid surgery) or staged embolization + resection or adjunctive embolization + resection/SRS or adjuvant SRS + resection are indicated for complex AVMs, such as giant AVMs involving deep eloquent areas, or AVMs with complex blood supply. (5) Conservation: conservation can be used for AVMs that are prone to severe disability due to intervention.

Unruptured AVMs: interventions are recommended if unruptured AVMs are assessed as being at high rupture risk or having refractory epilepsy or acceptable postoperative neurological deficits; otherwise, conservative treatment is recommended. The rupture risk stratification will be assessed qualitatively and quantitatively by the multidisciplinary team based on their own experience and the rupture prediction model to facilitate the division of the experimental and control groups. Regular multidisciplinary discussion meetings and fixed multidisciplinary groupings will ensure consistency of analytical results. Besides, the choice of intervention is the same as for ruptured AVMs.

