### Follow-up assessment

Neurofunctional status (mRS), subsequent hemorrhage, seizure, headache, novel neurofunctional deficit, and medication were queried at 3 months, annually (1 and 2 years), 3 years, and 10 years follow-up by trained research coordinators. Medical records and imaging examination data will be collected for suspected individuals with cerebral vascular events. An independent final review committee will assess suspected vascular events without hospitalization.

The MATCH study will conduct routine imaging follow-up by MRI, which is consistent with that described above. Due to the dose-cumulative effect, we will use DSA and MRI at the third year to determine the long-term obliteration rate, regardless of the intervention strategies. We will use imaging at 10th year after surgery to assess the ultra-long-term imaging prognosis. Color-coded DSA (follow-up DSA) was used to assess short-term and long-term time-dependent hemodynamic changes in residual nidus, peri-nidus, and cerebral hemispheres after treatment.

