### Outcomes measurements

The primary outcome: neurofunctional status (mRS score) at 3 years after treatment. The secondary outcomes: obliteration rate, subsequent hemorrhage, complication rate, and improvement in clinical symptoms (epilepsy, headache, neurological dysfunction) at 3 years after treatment. The obliteration rate will be evaluated by DSA or MRI, as several previous studies have suggested that MRI could provide a similar assessment of the obliteration rate as DSA [18]. The subsequent hemorrhage is defined as intracranial hemorrhage that could be attributed to AVM rupture with symptomatic and CT evidence. Postoperative complication included novel neurological dysfunction, radiation-related complications, etc. The prognosis of epilepsy will be assessed by Engle classification. Post-treatment headache will be assessed by the WHO pain grading classification.

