**Table 3 Tab3:** Baseline demographic and clinical characteristics of the participants in the MATCH study

Characteristics	All patients	Single-disciplinary cohort (2011.08–2021.04)	Multidisciplinary cohort (2018.06–2021.04)	*P* value
No. of patients	*N* = 3241	*N* = 2741	*N* = 500	
Ethnicity, male, n (%)	1911 (59.0)	1624 (59.2)	287 (57.4)	0.440
Age (years), mean ± SD	28.4 ± 14.6	28.3 ± 14.4	29.4 ± 15.6	0.118
Race, Han, n (%)	3109 (95.9)	2629 (95.9)	480 (96.0)	0.929
Onset manifestation				
Hemorrhage, n (%)	1984 (61.2)	1677 (61.1)	307 (61.4)	0.927
Seizure, n (%)	754 (23.3)	647 (23.6)	107 (21.4)	0.283
Headache, n (%)	698 (21.5)	587 (21.4)	111 (22.2)	0.695
Neurofunctional deficit, n (%)	583 (18.0)	488 (17.8)	95 (19.0)	0.522
Others, n (%)	271 (8.4)	230 (8.4)	42 (8.4)	0.995
Frequency of hemorrhage before admission, n	2268	1917	351	0.906
Type of seizure, generalized, n (%)	629 (19.3)	542 (19.7)	87 (17.4)	0.217
Duration from diagnosis to treatment (months), median, IQR	2.9 (0.9, 12.8)	2.8 (0.9, 12.9)	3.0 (0.9, 12.6)	0.471
Admission mRS, median, IQR	1 (1, 2)	1 (1, 2)	1 (1, 2)	0.653
Type of treatment				
Conservation, n (%)	491 (15.1)	412 (15.0)	79 (15.8)	0.659
Microsurgery, n (%)	1158 (35.7)	991 (36.2)	167 (33.4)	0.237
Embolization, n (%)	412 (12.7)	346 (12.6)	66 (13.2)	0.722
SRS, n (%)	480 (14.8)	413 (15.1)	67 (13.4)	0.334
Hybrid surgery, n (%)	141 (4.4)	120 (4.4)	21 (4.2)	0.858
Staged embolization + Microsurgery, n (%)	83 (2.6)	67 (2.4)	16 (3.2)	0.325
Embolization + SRS, n (%)	381 (11.8)	312 (11.4)	69 (13.8)	0.123
Microsurgery + SRS, n (%)	45 (1.4)	39 (1.4)	6 (1.2)	0.695
Microsurgery + Embolization + SRS, n (%)	50 (1.5)	41 (1.5)	9 (1.8)	0.612
Follow-up duration (years), median, IQR	5.6 (3.4, 7.9)	6.3 (4.4, 8.3)	2.4 (1.8, 3.3)	< 0.001^*^
Lost follow-up, n (%)	253 (7.8)	204 (7.4)	49 (9.8)	0.071
Patients who have completed 3 years follow-up, n (%)	2372 (79.4)	2181 (86.0)	191 (42.4)	< 0.001^*^

*IQR* Interquartile Range, *N* Denominator, *n* numerator, *MATCH* Registry of Multimodality treatment for brain ArTeriovenous malformation in mainland China, *mRS* Modified Rankin Scale, *SD* Standard Deviation, *SRS* Stereotactic Radiosurgery

^*^Statistical significance (*p* < 0.05)

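### Kaplan-Meier is the wrong display for time to complete obliteration after SRS if death or further curative treatment can come first; cumulative incidence should replace it

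*Protocol article*

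**What the plan says.** The protocol article, Statistical analysis, plans Kaplan-Meier plots for subsequent hemorrhage and for obliteration: "complete obliteration (for AVMs who underwent SRS) among different treatment modalities will be presented". The sentence before it mentions competing risks, but for another purpose: "competing risk analysis or NCC will be performed to explore the predictors of subsequent hemorrhage in the survival dataset". There it is one of several alternatives, alongside Cox regression. Nothing extends it to obliteration, and no rule is given for a patient who dies or is treated again before the nidus closes.

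Obliteration appears elsewhere in a different form. Outcomes measurements lists it at a fixed time: "The secondary outcomes: obliteration rate, subsequent hemorrhage, complication rate, and improvement in clinical symptoms (epilepsy, headache, neurological dysfunction) at 3 years after treatment". Follow-up assessment describes how it is measured: "we will use DSA and MRI at the third year to determine the long-term obliteration rate, regardless of the intervention strategies". Neither section says that this rate is taken from a Kaplan-Meier curve.

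Treatment combining SRS with surgery is foreseen. Clinical management includes the statement that "adjuvant SRS + resection are indicated for complex AVMs", and Table 3 has two rows in which SRS and microsurgery occur together.

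**The concern.** Kaplan-Meier knows two states, event or no event yet. Three things can end a patient's chance of obliterating through SRS without obliteration having happened: death, later resection of the irradiated nidus, and later curative embolization. The method can treat them in only two ways.

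- **Censor them.** The estimator then behaves as if these patients went on obliterating at the same rate as those still under observation. Someone who has died or no longer has a nidus cannot do so. One minus Kaplan-Meier is then never below the true cumulative incidence, and is above it as soon as such events occur while others go on to obliterate. The assumption is least plausible for resection prompted by SRS failure.
- **Count resection as the event.** The curve then mixes closure by SRS with removal by surgery.

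Neither gives the proportion obliterated by SRS. The curves are to be shown among treatment modalities, so unequal rates of death or further treatment would distort the contrast as well as the level. Under censoring, other things equal, the strategy with more competing events looks better than it is.

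**Working it through.** **Inputs from the article (Table 3).** SRS alone 480; embolization + SRS 381; microsurgery + SRS 45; microsurgery + embolization + SRS 50.

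- Any SRS: 480 + 381 + 45 + 50 = 956.
- Also recorded as having microsurgery: 45 + 50 = 95, and 95/956 = 9.9%.
- Check on the table: 491 + 1158 + 412 + 480 + 141 + 83 + 381 + 45 + 50 = 3241, the stated total.

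The article reports no obliteration rate, no deaths and no order of treatments, so there is no figure of its own to reproduce. The rates below are assumptions.

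**Calculation A: fix the curve reading.** Assume constant hazards over the horizon. Let p1 be the value read from one minus Kaplan-Meier, and p2 the probability of a competing event if obliteration did not intervene.

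- h1 = −ln(1 − p1), h2 = −ln(1 − p2)
- Cumulative incidence = h1/(h1 + h2) × [1 − (1 − p1)(1 − p2)]
- Excess = p1 − cumulative incidence
- Standard error for scale = √(p1(1 − p1)/n), here with n = 956: √(0.6 × 0.4/956) = 1.58 points

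With p1 = 60%, h1 = 0.916:

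| p2 | h2 | Cumulative incidence | Excess (points) | Excess in SE, n = 956 |
|---|---|---|---|---|
| 2% | 0.020 | 59.5% | 0.5 | 0.3 |
| 5% | 0.051 | 58.7% | 1.3 | 0.8 |
| 9.9% | 0.105 | 57.4% | 2.6 | 1.6 |

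The 5% row in full: 0.916/(0.916 + 0.051) × (1 − 0.40 × 0.95) = 0.947 × 0.62 = 0.587.

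**Calculation B: fix the true incidences.** Let F1 and F2 be the true cumulative incidences of obliteration and of the competing event.

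- H = −ln(1 − F1 − F2)
- One minus Kaplan-Meier = 1 − exp(−H × F1/(F1 + F2))

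With F1 = 60%, the curve reads 60.8% for F2 = 2%, 62.1% for 5% and 64.4% for 10%. Over F1 from 40% to 80% and F2 from 1% to 10%, the excess runs from 0.2 to 7.1 points. B gives larger values than A at the same nominal percentage, because in B that percentage is the share who actually have the competing event, which needs a higher underlying hazard.

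**Longer follow-up.** The error grows if competing events accumulate. By A, a curve at 70% with 10% competing events is 2.9 points too high, and one at 85% with 20% is 6.3 points too high. Both pairs of rates are illustrations; the article supports neither.

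**The case against.** The strongest reply is that the article does not say these patients are censored. It is a condensed account, and a rule for death and re-treatment may stand in the full protocol or analysis plan. That is fair, and it means a flat statement that the planned curve is too high would not be supported. It does not remove the point, because the article does fix the method, and Kaplan-Meier under either handling fails to give the proportion obliterated by SRS.

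Four stronger inferences are tempting, and the article does not support them.

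- **That the secondary outcome is biased.** The 3-year obliteration rate is described as an imaging assessment and is not said to be read from the curve. The point stops at the plots and their comparison. No log-rank test or other formal comparison of obliteration is named either.
- **That the 95 patients show salvage after failed SRS.** Treatment order is not reported. Surgery followed by SRS for a remnant is equally compatible with the table, and resection before SRS cannot compete with later obliteration. Clinical management presents the combination as a planned strategy for complex lesions. Where a curve describes that whole strategy, resection may legitimately belong to it.
- **That 9.9% can be applied to SRS alone.** None of the 95 is among those 480, nor among the 381 with embolization + SRS. It is an upper bound on recorded resection after SRS across the 956. It covers neither deaths nor later curative embolization.
- **That the larger long-term figures are findings.** They follow from assumed obliteration and competing-event rates.

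It also stands that with 2% competing events or fewer the 3-year error is small: 0.5 points by calculation A and 0.8 by B, at 60% obliteration.

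**Conclusion.** The concern holds in limited form. Kaplan-Meier is the named method for time to complete obliteration after SRS, and competing-risk analysis is not extended to that endpoint. If patients who die or are curatively treated by other means are censored, the direction of the error is certain: upward. If resection is counted as the event, the curve answers a different question.

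The size is uncertain. At a curve reading of 60% it is about 0.5 to 2.6 points for 2% to 9.9% competing events, under constant hazards and with rates that the article does not supply. That is about 0.3 to 1.6 standard errors for 956 patients. The change is worth making because a better method exists at almost no cost, and because the curves are meant for comparing modalities whose competing-event rates may differ.

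**What to change.** In Statistical analysis, replace the Kaplan-Meier plot of complete obliteration after SRS with a cumulative incidence function (Aalen-Johansen). Treat death, and unplanned later resection or curative embolization before obliteration, as competing events.

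Where resection is a planned part of the multimodality strategy being plotted, state whether the event is obliteration by SRS or by the strategy as a whole, and label the curve accordingly.

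If modalities are formally compared on this endpoint, use Gray's test, or cause-specific hazards reported beside the cumulative incidence.

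The cost is analysis wording and standard software. If the alternative was to censor these patients, the reported obliteration percentage will be slightly lower.
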